### Ethical Considerations

#### Ethics Committee Approval

The study protocol and related documents have been approved by the Ethics Review Committee of Shanghai Municipal Hospital of Traditional Chinese Medicine (approval 2025SHL-KY-70‐01), and have been filed with the ethics committees of the other 4 participating centers.

#### Informed Consent

Before screening, researchers will fully inform potential participants of the study’s purpose, methods, risks, benefits, and right to withdraw at any time. Only after the participants voluntarily sign the written informed consent form will they be included in the study. For participants with limited decision-making ability, informed consent will be obtained from their legal guardians.

#### Privacy and Confidentiality

All participant information will be anonymized and coded. The original data (including informed consent forms, case report forms [CRFs], etc) will be stored in a locked file cabinet, and electronic data will be stored in a password-protected computer. Only authorized researchers can access the data. During data analysis and publication, personal identifying information will not be disclosed.

#### Participant Compensation

Participants will receive free electroacupuncture treatment (or sham electroacupuncture treatment) and related examinations (such as actigraphy monitoring) during the study period. In addition, to compensate for the time and travel costs of participants, each participant will receive a subsidy of 100 yuan (6.70 yuan=US $1, representing the consensus average forecast for the study period, ie, mid‑2026 to December 31, 2027) after completing the entire study (including treatment and follow-up).

### Patients and Participants

#### Overview

We will inform the participants of the study protocol and obtain written informed consent before screening them according to the eligibility criteria. The included participants will be randomly allocated at 1:1 to receive 4-week electroacupuncture treatment (electroacupuncture group) or sham electroacupuncture treatment (sham electroacupuncture group). We will then conduct an 8-week follow-up for further observation. All procedures will rigorously adhere to the Declaration of Helsinki. The inclusion and exclusion criteria are described below.

#### Inclusion Criteria

First, male or female participants who were aged 18 years or older. This age limit is set because adults have relatively stable physiological functions and can better cooperate with the treatment and evaluation process.

Second, patients diagnosed with SM based on cytological or histopathological features, and undergone SM surgery within 1‐2 weeks. This time interval is determined because sleep disturbance after SM surgery is most prominent within 1‐2 weeks postoperatively, and intervention during this period is more conducive to improving rehabilitation outcomes.

Third, the PSQI score was >11. Patients with chronic insomnia disorder (defined as insomnia lasting ≥3 months before surgery) are excluded. According to the validation study of the Chinese version of PSQI, a score >11 indicates moderate to severe insomnia, which is a reasonable threshold for selecting patients with clinically significant postoperative insomnia [31,32].

Fourth, have an estimated survival period of at least 6 months. This is to ensure that participants can complete the entire treatment and follow-up process, and avoid the impact of patient death on the study results. The survival period is estimated by the attending physician based on the patient’s tumor type, stage, treatment response, and other factors.

Fifth, consent to participation and completion of the full treatment process, and provide written consent.

Sixth, postoperative blood examination showed no obvious abnormality, indicating that the patient’s general condition is stable and can tolerate electroacupuncture treatment.

Finally, no history of shift work in the past 6 months. Shift work can independently affect sleep patterns and confound the study results, so such individuals are excluded.

#### Exclusion Criteria

First, participants diagnosed with severe cardiovascular, hepatic, renal, hematopoietic, immune system diseases, or psychiatric disorders. These diseases may affect the safety of electroacupuncture treatment or interfere with the evaluation of study outcomes.

Second, those who have a history of other malignant neoplasms or concurrent other malignant tumors. Multiple tumors may lead to complex clinical symptoms and poor prognosis, which may confound the effect of electroacupuncture on insomnia.

Third, participants’ acupuncture area affected with skin infection, ulcer, and sores. These skin conditions may increase the risk of infection after acupuncture and affect the implementation of treatment.

Fourth, those who have mental disorders or sequelae of cerebral infarction leading to inability to take care of oneself or cooperate with treatment. Participants need to cooperate with acupuncturists during treatment and complete self-assessment scales, so good compliance is required.

Fifth, those who have consciousness, intelligence, language comprehension, and expression impairments. These impairments will affect the collection of outcome indicators (such as self-assessment scales).

Sixth, those who have sleep apnea syndrome. This disease is an independent cause of sleep disturbance, which may interfere with the evaluation of the efficacy of electroacupuncture on postoperative insomnia.

Seventh, those who have taken any sleeping pills, antidepressants, or antipsychotics within the past 2 weeks. These drugs may affect sleep status and lead to false results in efficacy evaluation.

Eighth, history of shift work in the past 6 months.

Finally, participants having chronic insomnia disorder (insomnia lasting ≥3 months) before SM surgery.

### Recruitment

The study will include 196 patients with insomnia. We will recruit patients through offline promotion and the hospitals’ official information platforms. Researchers will maintain contact with interested patients and conduct face-to-face interviews to gain a deeper understanding of their characteristics and specific situations. To enroll in the trial, participants need to be informed of the benefits and adverse reactions of this trial after being screened by the researchers in accordance with the inclusion and exclusion criteria. Participants have the right to withdraw from the study at any time.

### Sample Size Calculation

The sample size was estimated based on anticipated changes in PSQI scores. Based on previous trials among populations with CRI, the mean difference of PSQI between 2 groups is assumed to be 1.8 (SD 3.9) for both groups [28]. Through Power Analysis and Sample Size system (version 15.0.5) calculation, a sample size can provide 90% power to reject the null hypothesis with a significance level of 0.05 using a 2-sided 2-sample *t* test assuming equal variance. Considering the expected dropout rate of 20%, the final sample size is 196, with 98 patients in each group.

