#### Analysis of Primary and Secondary Outcomes (SPIRIT Item 20a)

##### Primary Outcome Analysis

The primary outcome is the change in PSQI total score from baseline (wk 0) to posttreatment (wk 4). ANCOVA will be used to compare the between-group difference in PSQI score changes, with baseline PSQI score, age, gender, tumor type, and participating center as covariates. This method can adjust for potential confounding factors and improve the statistical efficiency of the analysis.

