### Statistical Software and Significance Level

All statistical analyses will be performed using SPSS 26.0 (IBM Corp) or R 4.2.0 software (R Core Team). The 2-sided significance level will be set at α=.05, and no adjustment for multiple comparisons will be made for secondary outcomes to avoid type II errors, but the results will be interpreted with caution.

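### The 196 patients do not give 90% power after 20% dropout: on the plan's own inputs about 78 evaluable per arm give about 82%

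*Protocol article*

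**What the plan says.** The Sample Size Calculation section of the protocol article gives all the inputs. The effect and spread are: "the mean difference of PSQI between 2 groups is assumed to be 1.8 (SD 3.9) for both groups". The operating characteristics are "90% power to reject the null hypothesis with a significance level of 0.05 using a 2-sided 2-sample" t test with equal variances. The result is: "Considering the expected dropout rate of 20%, the final sample size is 196, with 98 patients in each group". The number of evaluable patients before the dropout allowance is not given.

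Other sections agree with these inputs. Under Statistical Software and Significance Level: "The 2-sided significance level will be set at α=.05". Under Patients and Participants, Overview: "The included participants will be randomly allocated at 1:1". The primary endpoint is the change in total PSQI from week 0 to week 4. The primary analysis differs from the test used for sizing: "ANCOVA will be used to compare the between-group difference in PSQI score changes", adjusted for baseline PSQI, age, gender, tumor type and center. Missing outcomes in the intention-to-treat analysis are handled by multiple imputation.

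**The concern.** The section presents 196 as a figure that already contains a 20% dropout allowance and still delivers 90% power. A standard two-sample calculation on its inputs gives almost the same number before any allowance. If so, the power claimed for the primary test holds only when nobody drops out, which contradicts the plan's own expectation.

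The stated power is what readers will use to interpret a null result. A non-significant primary comparison would be read as a 1-in-10 event if the true difference were 1.8, when on the stated test it would be nearer 1 in 5. The figure of 196 recurs in the Abstract, Recruitment, Results and Discussion, and the Discussion cites it in support of more reliable evidence. The article says recruitment had not begun at submission, so the statement can still be corrected before the trial starts.

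**Working it through.** **Inputs** (all from Sample Size Calculation): difference 1.8; SD 3.9 in each arm; two-sided alpha 0.05; two-sample t test, equal variances; power 90%; dropout 20%; 98 randomised per arm. Allocation is 1:1.

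**Step 1. Evaluable patients needed for 90% power.**

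Standardised difference: 1.8 / 3.9 = 0.4615.

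Normal approximation: n per arm = 2 × (1.960 + 1.282)² / 0.4615² = 98.65, so 99.

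Exact t test (noncentral t with 2n − 2 degrees of freedom and noncentrality 1.8 / (3.9 × √(2/n))): n = 99.6, so 100 per arm, 200 in total. Power is 90.1% at 100 per arm and 89.8% at 99.

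**Step 2. Trying to reproduce 98 per arm with 20% dropout.**

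| Setting | Evaluable per arm | n / 0.8 | n × 1.2 |
|---|---|---|---|
| Two-sided, 90% power, exact t | 100 | 125 | 120 |
| Two-sided, 90% power, normal | 99 | 124 | 119 |
| Two-sided, 80% power, exact t | 75 | 94 | 90 |
| One-sided, 90% power, normal | 81 | 102 | 98 |

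On the stated two-sided inputs neither form of inflation gives 98. The one combination tried that does give it is a one-sided test inflated by multiplication (81 × 1.2 = 97.2, rounded up). That contradicts the two-sided test stated in two places, and multiplying by 1.2 is not the correct inflation for 20% loss. The other possibility is that 98 is, within rounding, the two-sided number with no allowance. The article does not show which occurred, and the conclusion does not depend on it.

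**Step 3. Power that 98 per arm provides under the stated t test.**

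| Evaluable per arm | Basis | Noncentrality | Power (exact t) |
|---|---|---|---|
| 98 | no dropout | 3.231 | 89.5% |
| 88 | about 10% lost | 3.061 | 86.1% |
| 78 | 98 × 0.8 = 78.4 | 2.882 | 81.7% |

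The normal approximation at 78 gives 82.2%. Type II error is 100 − 81.7 = 18.3%, against 10% stated: a ratio of 1.8.

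**Step 4. What would be needed for 90%.**

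- Randomised with 20% dropout: 100 / 0.8 = 125 per arm, 250 in total, which is 54 more than 196.
- With 78 evaluable per arm: a true difference of 2.04 instead of 1.8, or an SD of 3.45 instead of 3.9.

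**Step 5. Could the planned ANCOVA close the gap?**

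The answer depends on the correlation rho between baseline and week-4 PSQI, which the article does not give, and on what the SD of 3.9 describes. The values below are assumptions: 78 per arm, equal variances at both visits, and only the baseline covariate counted. If 3.9 is the SD of the week-4 score, the residual SD is 3.9 × √(1 − rho²). If it is the SD of the change, the residual SD is 3.9 × √((1 + rho)/2).

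| rho | 3.9 = SD of week-4 score | 3.9 = SD of change |
|---|---|---|
| 0.3 | 85% | 94% |
| 0.4 | 88% | 93% |
| 0.5 | 91% | 91% |
| 0.6 | 95% | 89% |
| 0.7 | 98% | 87% |

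Power runs from 85% to 98% over this range, and the two readings move in opposite directions as rho rises. They agree only at 0.5.

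**The case against.** The strongest counter-argument is that the t test is not the primary analysis. Apart from the few degrees of freedom spent on covariates, ANCOVA has no larger residual variance than the unadjusted comparison. About 82% is therefore roughly a floor at 78 evaluable per arm, and the power of the analysis actually planned cannot be determined from the article. This stands as a limit on the claim: it cannot be said that the ANCOVA will have 82% power. It does not rescue the stated figure, because the 90% is tied explicitly to an unadjusted two-sample t test and no correlation is assumed anywhere.

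Two further points carry partial weight. First, the article does not say when the 20% dropout occurs. The primary endpoint is at week 4 and follow-up runs on for at least another 8 weeks, so fewer than 20% may be missing at week 4. If half the dropout came later (an assumption), 88 per arm would give 86%, still short of 90%. Second, multiple imputation keeps everyone in the intention-to-treat analysis and may recover some information where secondary outcomes are observed. It does not in general replace missing week-4 scores, and the plan itself treats dropout as needing an allowance.

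It is also fair to note that type I error, the estimated effect and the analysis method are unaffected.

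**Conclusion.** The concern holds. The article's own inputs contradict its sample size statement: 196 randomised with 20% lost gives 81.7% power for the stated t test, not 90%, and 90% would need 250. The shortfall of about 8 percentage points is too large for rounding, and neither the normal nor the exact method removes it.

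The 81.7% assumes that the full 20% is missing at week 4, that imputation restores nothing, and that the test is unadjusted as the section states. Less early dropout raises it, to 89.5% at most with none. Covariate adjustment could raise it to 90% or above, but only under a correlation the plan does not state. How 196 was arrived at cannot be settled from the document.

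**What to change.** Rewrite the sample size paragraph in one of two ways.

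1. Keep 196 and correct the power: 98 randomised per arm, about 78 per arm (156 in total) evaluable after 20% dropout, power about 82% for a 1.8-point difference with SD 3.9, two-sided two-sample t test at 0.05. Give the evaluable number so the dropout step can be followed.
2. If a figure near 90% is to be kept with 196, base it on the planned ANCOVA. State whether 3.9 is the SD of the change or of the week-4 score, give the assumed baseline to week-4 correlation with its justification, and show power over a range of correlations. At 0.5, 78 per arm gives about 91% on either reading. The correlation should come from data and not be chosen to reach 90%, particularly as entry at PSQI above 11 narrows the baseline range.

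The first option costs one paragraph and a less favourable stated power. The second adds an assumption that has to be defended. Neither needs more patients, provided that under the second the justified correlation does support the power claimed. If the sponsor instead wants 90% on the t test as written, the total is 250.

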### Randomization and Allocation Concealment

The random allocation scheme for this trial will be generated by The Clinical Research Center of Shanghai Municipal Hospital of Traditional Chinese Medicine, Shanghai University of Traditional Chinese Medicine. We will use stratified block randomization with centers as a stratification factor for group inclusion. When blocks are used up, centers will inform the data management center for replenishment. Independent investigators will place the treatment assignment code in consecutively numbered opaque envelopes based on the order of patients’ visits. All participants will be informed that they have the same probability of being assigned to the electroacupuncture group or the sham electroacupuncture group. Participants and researchers will not know the grouping in advance. To ensure the reliability of the research, all researchers will strictly abide by the principle of departmental separation and receive standardized training before implementation.

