### Blinding

This study adopts a single-blind (patient-assessor–blinded) method. Except for the acupuncturists, other personnel, including all participants, outcome assessors, data analysts, and statisticians, will be blinded to the patients’ grouping. To reduce communication and contact between patients, we will assign patients to receive treatment in different rooms. During the entire treatment period, patients should wear eye patches. Blind evaluation will be used by the evaluator to assess and record various observation indicators. To ensure the safety of the study data, we will set up a data safety monitoring committee in accordance with the guidance of the Data Safety Monitoring Board (DSMB). The data will ultimately be summarized by third-party blind statistical analysis.

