### Intervention

All study participants will be randomly assigned to either the electroacupuncture group or the sham electroacupuncture group in a 1:1 ratio, receiving treatment 3 times per week for 4 weeks. At the same time, we will keep records of actigraphy for patients at week 0, week 1, week 2, week 3, and week 4. Allocation of participants will be conducted by a licensed acupuncturist with more than 2 years of clinical experience. Except for the acupuncturists, the study investigators, participants, outcome assessors, study staff, and statisticians will all be blinded to the allocation. Before treatment, we will perform skin sterilization for patients. If patients experience severe physical discomfort due to insomnia, we will prescribe appropriate medication based on their conditions. During the medication period, we will strictly record the name, dosage, and administration method. Relevant investigators will also record the medication taken by patients on a CRF.

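### Centres report when blocks are used up and an unblinded acupuncturist conducts allocation, so some assignments can be deduced despite the assurance that grouping is not known in advance

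*Protocol article*

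**What the plan says.** Under Randomization and Allocation Concealment, the protocol article fixes the method ("We will use stratified block randomization with centers as a stratification factor for group inclusion") and how the list is topped up: "When blocks are used up, centers will inform the data management center for replenishment". The same section describes the concealment device, "Independent investigators will place the treatment assignment code in consecutively numbered opaque envelopes", adds a principle of departmental separation, and gives the assurance "Participants and researchers will not know the grouping in advance". The ratio is 1:1 (Patients and Participants, Overview: "The included participants will be randomly allocated at 1:1").

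The Intervention section says who allocates: "Allocation of participants will be conducted by a licensed acupuncturist with more than 2 years of clinical experience". The next sentence but none other in that section sets out blinding by role: "Except for the acupuncturists, the study investigators, participants, outcome assessors, study staff, and statisticians will all be blinded to the allocation". The Blinding section agrees: "Except for the acupuncturists, other personnel, including all participants, outcome assessors, data analysts, and statisticians, will be blinded".

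Block size, whether it is fixed or varied, and how many blocks are supplied at a time are not given. Withholding block size in a published article is normal and is not criticised here.

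**The concern.** Three stated procedures do not fit together. Centres can see when a supply of blocks is exhausted. The person conducting allocation belongs to the one role that knows which arm patients are in. Balance within each block means that past assignments carry information about the next one. Concealment then rests on the allocator not using what he or she can work out, whereas the article asserts that grouping is not known beforehand.

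The two sections also pull apart on who does what. One has independent investigators preparing the envelopes under departmental separation; the other has an acupuncturist conduct allocation.

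What is at stake is selective entry or selective timing of entry. Several eligibility criteria involve judgement (estimated survival, blood results without obvious abnormality), and one is a self-reported PSQI above 11. The primary outcome is change in the same self-reported PSQI. If entry were steered by a foreseen arm, the groups could differ in ways that covariate adjustment cannot be relied on to correct.

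**Working it through.** The article gives no predictability figure, so there is none to reproduce. The check asks what follows from the stated procedures and how large the effect could be.

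**Inputs from the article:** balanced 1:1 blocks within center; exhaustion reported by the center; allocation by an unblinded role; total sample 196 (Sample Size Calculation).

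**Assumed inputs:** block size b of 4, 6 or 8, with 2 and 10 as outer values.

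**Step 1: what follows with fewest assumptions.** Suppose a supply is made up of complete blocks, the allocator can see that one assignment is left, and he or she knows the earlier assignments in that supply. The arms must end level, so the last assignment is certain. This holds whatever the block sizes and however many blocks are in the supply.

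**Step 2: upper-end scenario.** Suppose every block boundary is visible, block size is fixed and known, and one person knows the full history. An assignment is certain once the other arm's places in the block are used up, so the number of certain assignments is the length of the final run of identical assignments. Over all balanced sequences the expected share is

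1 / (b/2 + 1).

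Check for b = 4: the six sequences AABB, ABAB, ABBA, BBAA, BABA and BAAB have final runs of 2, 1, 1, 2, 1 and 1. The sum is 8 out of 6 × 4 = 24 assignments, or 1/3.

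**Step 3: last assignment of each block only.** The share is 1/b.

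**Step 4: correct-guess rate** under the step 2 assumptions, always guessing the arm with more places left in the block (a coin toss when they are level), from full enumeration. Full concealment gives 50%.

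| b | Certain share, step 2 | Of 196 | Last only, step 3 | Of 196 | Correct guesses, step 4 |
|---|---|---|---|---|---|
| 2 | 50.0% | 98 | 50.0% | 98 | 75.0% |
| 4 | 33.3% | 65 | 25.0% | 49 | 70.8% |
| 6 | 25.0% | 49 | 16.7% | 33 | 68.3% |
| 8 | 20.0% | 39 | 12.5% | 24.5 | 66.6% |
| 10 | 16.7% | 33 | 10.0% | 20 | 65.3% |

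**Step 5: several blocks per supply.** If only the end of a supply of k blocks is visible, the guaranteed minimum is one assignment per supply, a share of 1/(k × b). With two blocks of 4, for example, that is 1/8 = 12.5%, against 25% when each block end is visible.

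**The case against.** The strongest reply is that the wording is loose and the route to harm is not shown. Much of this stands.

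- A reader might infer that centres learn where each block ends and hence its size. The text does not support that. Centres do the informing, and the plural leaves room for a supply of several blocks. If several or varying blocks are supplied, replenishment does not reveal block size; undisclosed varying sizes may already be in use.
- A reader might infer that the allocator is the treating acupuncturist and knows every earlier assignment. The text says only a licensed acupuncturist. With several at a centre, each may know part of the history. The sentence could even be a loose description of who delivers treatment.
- A reader might take 39 to 65 patients as the number affected. Those figures belong to an assumed scenario, and they count predictable assignments, not biased ones. Bias needs the person who can predict to influence who enters or when.
- Safeguards exist. Researchers do the screening (Recruitment), investigators and study staff are described as blinded, the envelopes are opaque and numbered, and Table 1 places screening and consent at week –1, before randomization at week 0.
- A reader might conclude that any selection bias could not be handled in the analysis. The primary ANCOVA adjusts for baseline PSQI, age, gender, tumor type and center, which covers part of the PSQI-threshold route.

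These points reduce the risk without removing it. Opaque envelopes do not stop deduction from past assignments. Nothing stated bars the allocator from influencing the timing of entry. Table 1 puts baseline PSQI and randomization in the same week without fixing their order. ANCOVA does not reach unmeasured characteristics.

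**Conclusion.** The point holds in limited form. The stated replenishment step and allocation by the only unblinded role together allow at least the last assignment before each replenishment to be deduced, provided the allocator knows the earlier assignments in that supply and can see that it is about to run out. That conflicts with the assurance on advance knowledge, and the Randomization and Intervention sections need to be reconciled.

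The size for this trial cannot be derived. The 20% to 33% range for blocks of 8 to 4 is an upper-end scenario resting on all three step 2 assumptions; 12.5% to 25% applies if only the last assignment of each block is counted; a multi-block supply lowers it further. Nothing in the article shows that selection would occur. The fault lies in procedures the article states, not in detail it leaves out, and correcting it is a cheap improvement.

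**What to change.** 1. Have the Clinical Research Center that already generates the scheme produce each center's full list up front, with randomly varying block sizes not disclosed to the centers, and long enough that no center is expected to reach its end.
2. Delete the step in which centers trigger replenishment.
3. Amend the Intervention section so that the independent investigators who already handle the envelopes, and not an acupuncturist, release each assignment, and only after consent, eligibility and baseline PSQI are recorded. The acupuncturist is then told only that patient's arm.

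The cost is a change of wording and a longer list, using staff already named and no extra patients or visits. The statistical downside is a slightly larger possible imbalance within a center when recruitment stops part-way through a block: at most half the size of that block, for example 4 patients for a block of 8. Recruitment is still described as prospective, so the change can be made before the first patient is randomized.
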